### Antenatal measures - maternal

Maternal body weight is measured to the nearest 0.1 kg using calibrated electronic scales (Tanita, USA). Maternal height is measured to the nearest millimetre using a fixed wall Harpenden Stadiometer (Holtain Ltd., Crymych, UK). Resting heart rate and resting blood pressure are measured using standard protocols [28].

Aerobic fitness testing is carried out using a sub-maximal graded exercise test on an electronically-braked cycle ergometer (Schiller, Baar, Switzerland), with simultaneous breath-by-breath measurement of expired and inspired O_2_ and CO_2_ gas volumes (ParvoMedics TrueOne 2400 Metabolic Measurement System, Parvomedics, Sandy, Utah, USA) to a target heart rate of 150 beats per minute, as previously described [22]. The test begins with a workload of 30 W and increases by 10 W every minute until a target heart rate of 150 beats per minute is reached. Participants are instructed to maintain a constant cycling speed at 60 rpm throughout the test. Parameters of interest include time taken to reach the peak heart rate of 150 bpm, workload (W) when reaching peak heart rate, and peak VO_2_.

Maternal quality of life is measured using a self-administered questionnaire, the WHO Quality of Life-BREF (WHOQOL-BREF) version, which consists of a total of 26 questions in 4 domains [29]. Maternal physical activity levels are measured using the Pregnancy Physical Activity Questionnaire (PPAQ). The PPAQ is self-administered and asks respondents to report the time spent participating in 32 activities, including household/caregiving, occupational, sports/exercise, transportation, and sedentary activities [30]. The total weekly energy expenditure in MET-h/week is measured. Dietary data from 3-day food records completed at baseline and mid intervention are analysed using Foodworks 7 Professional edition (Xyris Software, Australia). Data are entered into the database by a single investigator blinded to group allocation, and analysed for total energy intake as well as% energy from protein, fat, and carbohydrate.

### Antenatal measures - offspring

Measurement of fetal growth are performed using standard obstetric ultrasound techniques by a single investigator, blinded to group allocation, at a single medical institution in Auckland (Middlemore Hospital, Counties Manukau District Health Board). All scans are performed utilising a single Philips IU22 ultrasound scanner (Philips Ultrasound, Bothell, USA) with 3D capability. The ultrasound transducer adopted is the Philips curvilinear array (C5-1, Philips Ultrasound, Bothell, USA) while the 3D transducer is a mechanical curved-array 3D abdominal ultrasonic transducer (3D 6–2 Philips Ultrasound).

Standard growth measurements including biparietal diameter (BPD), head circumference (HC), humerus diaphyseal length (HDL), abdominal circumference (AC), and femur diaphyseal length (FL) are performed according to the protocols published by the Australasian Society for Ultrasound in Medicine [31]. At each examination, all measurements are obtained three times from three separately generated ultrasound images, and then averaged. The standard measurements are used to calculate estimated fetal weight (EFW) by the Hadlock 4 equation [32]. Scans are recorded electronically for later analysis of other measures of fetal growth and fat deposition. Soft tissue growth is assessed by measurements taken from the 3D volume dataset including thigh circumference (ThC), partial thigh volume (TVol), arm circumference, (ACirc) and partial arm volume (AVol) as described by Lee [33]. The 3D volume measurements are obtained by averaging three measurements from three manipulations of the one data set offline. Volume analysis is done offline using Philips QLAB™ software version 6. Measurements of fetal fat mass are calculated by taking the total cross-sectional limb area and subtracting the central lean area, as previously described [34].

Between-group comparisons of fetal growth will include measures of BPD, HC, AC, HDL, FL and EFW at 24, 28, 32, and 36 weeks of gestation. Between-group comparisons of fetal body composition will include measures of ThC, TVol, ACir, AVol and estimated fat mass at 28, 32, and 36 weeks of gestation.

### Postnatal measures

Newborn weight, length, and head circumference measured at birth are obtained from medical records. Data on Apgar scores at 1 and 5 minutes after birth, neonatal hypoglycaemia needing intravenous treatment, neonatal hyperbilirubinaemia requiring treatment, presence of birth injuries, congenital anomalies, admission to neonatal intensive care or special care units, and length of hospital stay following delivery are also collected. Neonatal anthropometry (weight, length, and head circumference) are measured by a single investigator at the Maurice and Agnes Paykel Clinical Research Unit at 14 ± 2 days after delivery. Neonatal weight is measured to the nearest 10 g using electronic scales (Tanita 1583, Tanita Corp). Neonatal length is measured using a Holtain neonatometer. Occipito-frontal head circumference is obtained to the nearest millimetre using a flexible non-stretchable tape. BMI is calculated as weight/height^2^ (kilograms/metre^2^). Ponderal index is calculated as weight in grams × 100 divided by the cube of length in centimetres.

Maternal and neonatal body composition and bone density are evaluated at 14 ± 2 days after delivery by whole-body dual-energy absorptiometry (DXA, Lunar Prodigy 2000, General Electric, Maddison, Wisconsin, USA), by a single investigator at the Maurice and Agnes Paykel Clinical Research Unit. All scans are analysed by the same operator, utilising Encore 2007 software v.11.40.004 including paediatric software packages (GE Corp., Madison, WI, USA). Quality control checks are performed on a daily basis prior to scanning, using a standard block provided by the manufacturer.

### Metabolic markers

Maternal blood samples collected at baseline and at the end of intervention are processed and stored at the Liggins institute. Venous cord blood is collected at delivery by the lead maternity carer, who is instructed beforehand on the procedure. Cord blood samples are processed within 3 hours of collection and stored at -80°C at hospital laboratories. We plan to analyse maternal and cord blood samples at the end of the study. Parameters that will be assessed include: insulin-like growth factors I (IGF-I), IGF-II, insulin-like growth factor binding protein 1 (IGFBP-1), IGFBP-3, leptin, adiponectin, interleukin 6 (IL-6), tumour necrosis factor α (TNF α), insulin, glucose, highly sensitive C-reactive protein (CRP), triglycerides, total cholesterol, high-density lipoprotein cholesterol (HDL-C), low-density lipoprotein cholesterol (LDL-C) and free fatty acids. Sex hormone-binding globulin (SHBG) will also be measured in maternal samples as a surrogate measure of insulin resistance. Samples will be preserved for future metabolomics studies.

### Statistical considerations

#### **
*Sample size*
**

Based on a previous exercise intervention performed by our research group in Auckland using similar methodology [22] and using birth weight as the primary outcome, a total sample size of 100 women (n = 50 per group) will provide 80% power at 5% level of significance (two-sided) to detect a group difference of 250 g or more, assuming a standard deviation of 430 g [22].

#### **
*Data analyses*
**

Statistical analyses will be performed using SAS version 9.3 (SAS Institute Inc. Cary NC). All statistical tests will be two-tailed and a 5% significance level maintained throughout the analyses. Study data are entered into an Excel database, and then imported into SAS for final analysis.

#### **
*Baseline characteristics*
**

Baseline characteristics will be summarised using descriptive statistics. Continuous variables will be described as numbers of observed and missing values, mean, standard deviation, median, minimum and maximum. Categorical variables will be described as frequencies and percentages. Results will be presented for each of the two treatment arms as well as overall. Since any differences between randomised groups at baseline could only have occurred by chance, no formal significance tests will be conducted.

#### **
*Treatment effects*
**

Treatment evaluation will be performed on the principle of intention to treat (ITT), using data collected from all randomised participants. Analysis of covariance (ANCOVA) regression models will be used to evaluate the main treatment effect on the primary outcome between the two treatment groups, adjusting for parity and maternal ethnicity (i.e. stratification factors). A similar approach will be used for other continuous secondary outcomes, with the baseline outcome (if measured) added to the model as a confounding variable. Model-adjusted means and their difference between two groups will be estimated and tested. Logistic regression model will be used for the analysis of a binary outcome (i.e. yes or no), with associated odds ratio and 95% confidence interval. In addition to the intention to treat analysis, a per protocol (PP) analysis will also be undertaken on those participants who have no major protocol violations.

Reporting will adhere to the CONSORT guidelines for reporting parallel group randomised trials [35,36].

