### Participants

Pregnant women aged 18 to 40 years with a BMI ≥25 kg/m^2^ who are carrying a singleton fetus less than 20 weeks of gestation, with gestation confirmed by a dating scan early in pregnancy, and who are resident in the Auckland region are eligible for the trial. Exclusion criteria include ongoing smoking during the current pregnancy or contra-indications to aerobic exercise in pregnancy as stated by the American College of Obstetricians and Gynaecologists [24].

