### Secondary outcomes

Offspring outcomes include neonatal anthropometry and body composition, fetal growth measures, cord blood metabolic markers and newborn complications including rates of large-for-gestational-age (birth weight >90^th^ centile) and small-for-gestational-age (birth weight <10^th^ centile) babies. Maternal outcomes include weight gain, aerobic fitness, quality of life, metabolic markers, post-partum weight and body composition, as well as pregnancy and delivery outcomes including timing and mode of delivery and length of hospital stay.

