### Clinical assessments/Data collection

Each participant visits the Maurice and Agnes Paykel Clinical Research Unit (Liggins Institute, Auckland) for three study assessments. The first visit for the baseline assessment occurs at 19 ± 1 weeks of gestation and the second visit at 36 ± 1 weeks of gestation. During the first visit, participants complete consent forms and fill in questionnaires on demographic, medical and obstetric history. The other procedures are similar for both first and second visits, where each participant’s weight, height, resting heart rate, resting blood pressure, HbA1c, and baseline aerobic capacity are assessed by a single investigator. Blood samples are collected and stored for metabolic testing. Participants complete a quality of life assessment questionnaire and the physical activity questionnaire and 3-day diet records are collected. At the second visit participants receive a pack with instructions for collection of cord blood by delivery staff.

During the intervention period, participants in both groups undergo regular ultrasound scans for research purposes at 4-week intervals starting from 24 ± 2 weeks of gestation. Participants are requested to maintain daily records of any leisure time physical activity/exercise they engage in between 20 weeks of gestation up to delivery on exercise diaries provided by the study. Participants also complete 3-day food intake records and a physical activity questionnaire at baseline prior to randomisation and midway though the intervention at a time when exercise prescription is maximal (32 weeks of gestation), to assess any group difference in these measures.

The final study visit occurs at 14 ± 2 days after delivery. Maternal weight and neonatal anthropometry (weight, length and occipito-frontal head circumference) are recorded, and both mother and baby have body composition assessed by DXA scans. Pregnancy, delivery and newborn data (including feeding history) are obtained from the participants and hospital records. Study exercise diaries and heart rate monitors are also collected at this point.

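### Maternal DXA outcomes have no baseline value, so the stated covariate rule leaves them unadjusted for maternal size, although baseline weight and height are collected

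*Protocol article*

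**What the plan says.** The protocol article lists "post-partum weight and body composition" among the maternal secondary outcomes (Secondary outcomes). The measurement is described under Postnatal measures: "Maternal and neonatal body composition and bone density are evaluated at 14 ± 2 days after delivery by whole-body dual-energy absorptiometry". Clinical assessments/Data collection agrees. At the final visit "both mother and baby have body composition assessed by DXA scans", and no scan appears at an earlier visit. At the 19 ± 1 and 36 ± 1 week visits the measurements are "weight, height, resting heart rate, resting blood pressure, HbA1c, and baseline aerobic capacity are assessed by a single investigator".

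Statistical considerations (Treatment effects) sets the model. The primary outcome is analysed by ANCOVA, "adjusting for parity and maternal ethnicity (i.e. stratification factors". Other continuous outcomes follow a similar approach, "with the baseline outcome (if measured) added to the model as a confounding variable".

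Two design features bear on maternal size. Eligibility is "Pregnant women aged 18 to 40 years with a BMI ≥25 kg/m^2", with no upper limit stated (Participants), and randomisation is stratified on parity and ethnicity only (Randomisation).

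**The concern.** The rule makes adjustment depend on whether the same variable was measured at baseline. That works for post-partum weight, which has a 19-week value. It fails for fat mass, lean mass, percent fat and bone density from the maternal scan, which have none. Two results of one visit are therefore handled differently: body weight is adjusted for baseline weight, while the fat and lean mass that make up that weight are not.

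An open-ended BMI criterion allows a wide spread in maternal size at entry, and nothing in the allocation balances it. A difference in body composition between groups must then be seen against that spread. If the groups happen to differ in size at baseline, the unadjusted contrast carries part of that difference. A prognostic covariate that could deal with both is already recorded before randomisation. Adding it only after the results are known would be open to challenge as a post hoc choice, so it is better fixed in advance.

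**Working it through.** **The plan's own figure.** The only sample size calculation is for birth weight: "a total sample size of 100 women (n = 50 per group" and closing bracket, for a 250 g difference, SD 430 g, two-sided 5%, 80% power. The normal formula is n per arm = 2(1.960 + 0.842)² × 430² / 250² = 46.4, so 47. The t-based figure is 48. Power at 50 per arm is 82.8% (normal) or 82.1% (t). The stated 50 is consistent with rounding up. The article gives no figure for maternal body composition.

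**Inputs for the DXA outcomes.**
- 50 analysed per arm (the article states no dropout allowance), two-sided 5%, 80% power.
- r, the correlation between baseline maternal size and the DXA outcome. This is an assumption, shown over 0.3 to 0.9.
- Differences are expressed in units of the outcome's SD without size adjustment, because the article gives no SD for any DXA measure.

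**Unadjusted detectable difference.** (1.960 + 0.842) × √(2/50) = 2.802 × 0.20 = 0.56 SD.

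**With baseline size in the model.** Residual variance is multiplied by 1 − r², the detectable difference by √(1 − r²), and the equivalent unadjusted sample size is 50/(1 − r²) per arm.

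| Assumed r | Variance removed | Detectable difference (SD) | Equivalent n per arm |
|---|---|---|---|
| 0.3 | 9% | 0.53 | 55 |
| 0.5 | 25% | 0.49 | 67 |
| 0.7 | 49% | 0.40 | 98 |
| 0.8 | 64% | 0.34 | 139 |
| 0.9 | 81% | 0.24 | 263 |

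**Thresholds.** More than half the variance is removed only if r² > 0.5, that is r > 0.71. The standard error is halved only if 1 − r² < 0.25, that is r > 0.87.

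**Allowing for parity and ethnicity.** Suppose these already explain 10% of the variance (assumption) and r² is the total explained once size is added. The further reduction is 1 − (1 − r²)/0.90:
- r = 0.5: 1 − 0.75/0.90 = 17%
- r = 0.7: 1 − 0.51/0.90 = 43%
- r = 0.8: 1 − 0.36/0.90 = 60%
- r = 0.9: 1 − 0.19/0.90 = 79%

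**Chance imbalance.** The standard error of the baseline difference in size between arms is √(2/50) = 0.20 SD. An imbalance of at least 0.20 SD, one standard error, occurs in about 32% of trials. At r = 0.8 it moves the unadjusted contrast by 0.8 × 0.20 = 0.16 SD, which is 0.16/0.56 = 29% of the unadjusted detectable difference. Adjustment removes that component.

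**The case against.** The strongest reply is that nothing here is invalid. ANCOVA on the stratification factors, plus the baseline outcome where it exists, is an unbiased analysis of a randomised trial. The article is also a condensed account with one general sentence for all continuous secondary outcomes, and a full analysis plan could add covariates. The outcome is one item in a long secondary list, in a trial whose stated main focus is offspring health.

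The validity point stands, and it sets the limits of this comment. The point about condensation stands only in part. The article does not merely leave the covariates open. It states which ones enter and on what condition, and that condition cannot be met for a named outcome. An analysis plan written to follow it would carry the gap forward.

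Two stronger readings are tempting, and the document supports neither.
- A reader might infer that most of the achievable precision is thrown away. That needs r above about 0.71, and the article gives no correlation, no SD for any DXA measure and no BMI distribution. Such a value is plausible for total fat mass in a cohort with no BMI ceiling. It is unsupported for percent fat and bone measures.
- A reader might infer that a chance imbalance in BMI would bias the treatment effect. Over repeated randomisations it does not: the unadjusted standard error and the 5% error rate already allow for it. The issue is the influence of an imbalance in the one trial that is run, and the wider interval.

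**Conclusion.** The point holds as a matter of efficiency. As written, the rule leaves the maternal DXA outcomes adjusted for parity and ethnicity only, while baseline weight and height are scheduled for every woman before randomisation and go unused. The avoidable residual variance is 9% to 81% over assumed r of 0.3 to 0.9, and its place in that range will differ between the DXA measures. These figures rest on 50 analysed women per arm, a linear relation with a common slope, and r being the correlation that remains after parity and ethnicity. If those factors already explain part of the variance, the further gain is somewhat smaller. Birth weight and post-partum weight are not affected.

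**What to change.** Amend the covariate rule before the data are analysed. The maternal DXA outcomes (fat mass, percent fat, lean mass, bone measures) have no baseline value, so their models should include maternal weight and height from the 19-week visit, or BMI derived from them, in addition to parity and ethnicity. Choose weight and height or BMI now, and state the functional form (linear, for example), so that the choice cannot depend on the results.

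The cost is one sentence in the analysis plan. No new measurement, visit or procedure is needed. Even if size proved weakly related to an outcome, two extra covariates would use only two residual degrees of freedom in a trial of 100.

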## Discussion

This randomized controlled trial has several unique characteristics. First, it utilises a non-weight bearing home-based antenatal exercise intervention, previously applied to non-obese women [22]. This will enable direct comparison of outcomes of a similar exercise intervention in obese and lean women. Secondly, the main focus of this antenatal exercise trial is on offspring health, with longitudinal assessments of fetal growth and body composition during the intervention period, as well as measures of newborn anthropometry and adiposity. While a number of randomised controlled trials of prescribed antenatal exercise have been conducted over the last three decades, their primary focus has been on maternal health and there is a lack of robust evidence on the effects of antenatal exercise on offspring health (18, 23). Furthermore, while there is some evidence of positive long-term effects of antenatal exercise for offspring of lean mothers (20), long-term effects on offspring of overweight or obese mothers appear to have received little attention. Therefore, this trial also aims to establish a cohort of overweight /obese mothers and offspring with well-documented antenatal and perinatal data to be followed up to determine the long-term effects of antenatal exercise on offspring and maternal health. As a result, this study addresses the lack of prospective robust data on the effects of antenatal exercise on short- and long-term outcomes of mothers and their offspring (43).

Another feature of this trial is the use of methods to enhance and monitor compliance to prescribed exercise. Many antenatal exercise interventions, especially those involving overweight and obese women have encountered problems with compliance [37,38]. This may be partly attributed to the general tendency for physical activity levels to decline during pregnancy [39,40], especially in mothers who are obese [41,42], However, many previous exercise studies have also failed to report adequately on compliance with interventions [18]. Previous studies have suggested that home-based exercise interventions can lead to increased compliance, as they enable exercise to be undertaken in a comfortable and familiar environment [43]. Therefore, a home-based intervention was chosen, to enhance feasibility of regular exercise, and improve compliance to the exercise protocol. Previous home-based stationary cycling interventions in non-obese [22] and obese [43] pregnant women have reported high acceptance and good compliance levels. Furthermore, during pregnancy, non-weight bearing exercises may be better tolerated, minimizing joint and musculoskeletal stress [44], and stationary cycling can be especially suitable for overweight or obese women, who are likely to continue to gain extra weight with advancing pregnancy. In addition, exercise prescription in our study has been modified to suit sedentary overweight and obese pregnant women, with gradual progressive increase in frequency and duration in keeping with recommendations [44], while maintaining moderate intensity based on target heart rates specific for this group [25].

While this study has been designed to optimise compliance, it remains essential to have objective assessment of compliance. This has been absent from many exercise intervention trials, making assessment of benefits problematic. In this study, we are using downloadable heart rate monitors. Not only does this provide evidence of exercise intensity, but also evidence of compliance that can be used in outcome analysis.

In summary, the proposed study will provide a platform to objectively assess a non-weight bearing exercise regime on overweight and obese women pregnant women, provide quantitative outcome data on them and their babies, and lead to an offspring cohort that can be followed throughout childhood.

